### Statistical methods

Analyses will be performed using commercially available software (IBM SPSS Statistics 23, SPSS Inc., Chicago, IL, USA). All data derived from the statistical methods will be given in mean ± standard deviation. Research shows that the most successful athletes in marathon and ultra-marathon running events are frequently those who lose substantially more than 3–4 % BW during competition (Zouhal et al. 2011). Mean body weight of male recreational marathon runners is 73.9 ± 8.1 kg (Barandun et al. 2012) and 75.8 ± 8.6 kg (Friedrich et al. 2014) of male recreational half marathon runners. Mean body weight of female recreational runners is 59.1 ± 6.3 kg (Rüst et al. 2013) and 60.1 ± 7.8 kg (Friedrich et al. 2014) of female recreational half marathon runners. Expected body weight loss during a marathon race is 2.3 ± 2.2 % overall (Zouhal et al. 2011). For male recreational marathon runners we expect a 2.3 % weight loss from 73.9 to 72.2 kg, therefore a sample size of 179 runners is needed to reach 80 % power with two-sided test and alpha of 0.05. For female recreational marathon runners we expect a 2.3 % weight loss from 59.1 to 57.7 kg, therefore a sample size of 159 runners is needed to reach 80 % power with two-sided test and alpha of 0.05. Since body weight loss during a marathon is inversely related to race finishing time (Zouhal et al. 2011) we expect the fastest runners to lose the most relative body weight during competition. Multi-variant regression analyses will be used the determine effects of kind of diet, sex, age, BMI, finished running distances, years of race experience, weekly training load, weekly training frequency, training intensity, in-race food and fluid consumption on individual finishing time (% of overall winners time, ranking, calculated pace). An analysis of variance will be performed to compare individual finishing time (% of overall winners time, ranking, calculated pace), sex, age, body weight, height, BMI, attended running events in past 2 years, finished running distances, personal best time on each distance, number of planned events for 2014/2015, daily/weekly training frequency, daily/weekly training load, period of preparation for main event, aim of race participation, years of running experience, motivation for running then and now, assisted training, years of race experience, training intensity, medium/long-term goal of racing, additional specific kinds of training, specific diet including supplements, specific training/diet prior to race, diet on day of rest/training/race, pre/in/post-race diet, in-race food and fluid consumption, specific gear, relevant medical measures, pre/post-race body weight (including clothing and shoes), calculated weight loss, in-race: nutritional strategy during race, fluid and nutrient intake including breakfast, mood status, and RPE (Borg) whole body/respiratory/legs, among the three subgroups created respective to diet.

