### Trial objectives

The first and major goal of the NURMI Study is to compare endurance performance of vegetarian and vegan runners to non-vegetarian marathon runners and to determine potential differences/to identify possible correlations.The second goal is to investigate the prevalence of vegetarian and vegan runners in endurance (half-marathon and marathon) events.The third goal is to validate the subjects self-reports on his/her dietary behavior.

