### Outcomes

#### Primary outcomes

In addition to running performance (individual marathon finishing time of Step 3) adjusted to performance level the primary outcome is the prevalence of kinds of diets (omnivorous, vegetarian, vegan) among runners attending running events.

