### Strengths of the study

Since scientific data about endurance and ultra-endurance athletes following a vegan diet is limited the NURMI Study will be the first study to assess this issue considering a bigger sample size. The NURMI Study aims to provide a large data set comparing respective subgroups of omnivorous, vegetarian and vegan runners ranging from epidemiological aspects, dietary and training habits, in-race dietary consumption, and performance measurements. Large numbers of participants will allow to discriminate between and, identify associations with, different dietary patterns and level of training status as well as to detect differences in running performance between subgroups of omnivores, vegetarians and vegans. To make sure to assess fit runners only the NURMI Study focuses on runners who are at least capable of coping the half-marathon distance as the primary inclusion criteria.

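### The only sample-size statement (179 men, 159 women, 80 % power) concerns a secondary weight-loss outcome, appears to use the wrong SD, and does not support the claim about performance differences between diets

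*Protocol article*

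**What the plan says.** Under Trial objectives the article states: "The first and major goal of the NURMI Study is to compare endurance performance of vegetarian and vegan runners", with non-vegetarian marathon runners as the comparator. Under Primary outcomes it names "running performance (individual marathon finishing time of Step 3) adjusted to performance level", together with the prevalence of the three diets. Calculated weight loss appears under Secondary outcomes, among the Step 3 items.

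The only sample-size reasoning is in Statistical methods, and it is about weight:

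- Men: "For male recreational marathon runners we expect a 2.3 % weight loss from 73.9 to 72.2 kg", followed by "therefore a sample size of 179 runners is needed to reach 80 % power with two-sided test and alpha of 0.05".
- Women: "For female recreational marathon runners we expect a 2.3 % weight loss from 59.1 to 57.7 kg", followed by "therefore a sample size of 159 runners is needed to reach 80 % power with two-sided test and alpha of 0.05".
- Variability: the between-runner SDs of body weight are given as 8.1 kg (male marathon runners) and 6.3 kg (female runners). The loss itself is given separately: "Expected body weight loss during a marathon race is 2.3 ± 2.2 % overall". The text does not say which SD entered the calculation.

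The paragraph then notes that weight loss and finishing time are inversely related, and goes on to the regression on finishing time and the analysis of variance across the three diet groups. Strengths of the study says that large participant numbers will allow the study to separate dietary patterns "as well as to detect differences in running performance between subgroups of omnivores, vegetarians and vegans".

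**The concern.** Two things look wrong.

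First, a loss from start to finish is a change within the same runner. Its precision depends on how much that change varies between runners, not on how much runners differ in body weight. If 8.1 and 6.3 kg were used, the stated sizes and the stated 80 % do not belong together.

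Second, the calculation answers a question other than the study's main one. It contains no diet groups and no finishing time. Yet it is the only power statement in the article, and it stands directly before the diet-group analyses of finishing time. At stake is what the study may claim. The article asserts that its size will reveal performance differences between diets, and no figure in it bears on that assertion.

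**Working it through.** **Inputs** (all from Statistical methods unless noted)

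- Two-sided alpha 0.05 and power 80 %: z = 1.960 and 0.842, sum 2.802, squared 7.849.
- Difference in men: 73.9 − 72.2 = 1.7 kg. Difference in women: 59.1 − 57.7 = 1.4 kg.
- Between-runner SD of weight: 8.1 kg (men), 6.3 kg (women).
- SD of the loss: 2.2 % of body weight, reading the ± as a standard deviation. This is 0.022 × 73.9 = 1.63 kg in men and 0.022 × 59.1 = 1.30 kg in women.
- German population shares (Background): 10 % vegetarian, 1.1 % vegan. Used only for the illustration in step 4.

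**1. Reproducing the stated figures.** One-sample normal formula, n = 7.849 × SD² / difference²:

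- Men: 7.849 × 8.1² / 1.7² = 178.2, rounded up to 179.
- Women: 7.849 × 6.3² / 1.4² = 158.9, rounded up to 159.

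Both match exactly. Of the other versions tried with the same SDs, the exact t-test gives 181 and 161, a one-sided test 141 and 126, 90 % power 239 and 213, and a two-independent-group formula 357 and 318 per group. None gives 179 and 159.

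**2. What that SD implies.** With equal SDs before and after, SD of change = SD × √(2(1 − r)), where r is the before-after correlation. Setting the SD of change equal to the between-runner SD requires r = 0.5. The article's own 2.2 % implies r = 1 − 1.63² / (2 × 8.1²) = 0.98 in men and 1 − 1.30² / (2 × 6.3²) = 0.98 in women.

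**3. The weight test with the article's SD of change.**

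- Normal approximation: men 7.849 × 1.63² / 1.7² ≈ 7.2; women 7.849 × 1.30² / 1.4² ≈ 6.8.
- Paired t-test (noncentral t): 10 men and 9 women.
- Ratio to the stated sizes: 179 / 10 ≈ 18 and 159 / 9 ≈ 18.
- Power at 179 men or 159 women: above 99.9 %.
- Sensitivity: the 2.2 % is an overall literature figure, and here runners weigh themselves in clothing and shoes. If that doubled the SD (an assumption), the paired t-test would need about 31 men and 30 women, still far below the stated sizes.

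**4. The diet comparison (illustration only).** The article gives no effect size or SD for finishing time, no total and no diet split, so no required size can be computed. Suppose the total were 179 + 159 = 338. The pairwise difference detectable with 80 % power, two-sided 0.05, without covariates or multiplicity adjustment, is 2.802 × √(1/n₁ + 1/n₂) in SD units:

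| Assumed split (omnivore / vegetarian / vegan) | Vegetarian vs omnivore | Vegan vs omnivore |
|---|---|---|
| Equal thirds (about 113 each) | 0.37 SD | 0.37 SD |
| German population shares (about 300 / 34 / 4) | 0.51 SD | 1.41 SD |

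The same total thus gives nearly a fourfold range for the vegan contrast (1.41 / 0.37 ≈ 3.8). The stated numbers do not fix the power of the main comparison.

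**The case against.** The strongest reply has five parts.

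*The SD is inferred.* True: the text names none. But an exact match in both sexes, with each sex's own SD and the rounded weights as printed, makes another origin unlikely.

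*The error is on the safe side.* Also true. It inflates the size for the weight test, so no weight-loss conclusion is put at risk. Taken alone, the SD error would be minor.

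*Weight loss is tied to the main question.* The planned analysis of variance does compare calculated weight loss across the diet groups, so it would be wrong to say that this outcome has nothing to do with diet. It is the sample-size calculation that leaves diet out. The stated link between weight loss and finishing time is a correlation. It supplies neither an effect size nor an SD for a diet contrast in finishing time.

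*The numbers are minimum requirements by sex, not the study's size.* This stands. The article plans to enrol a large number of runners and sets no total; 338 is only the sum of the two figures.

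*The population split is pessimistic.* This stands in part. A reader might infer that the study has been shown to have almost no power for vegans, so that a null vegan result must be uninformative. The documents do not support that. The shares describe the German general population, while recruitment runs partly through vegetarian magazines and could raise vegan numbers. The article expects vegetarians and vegans to be rarer at running events than in the population, but that is a prediction about events, not about this volunteer sample. Covariate adjustment would also lower the detectable differences in raw SD units.

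That a journal article condenses a fuller protocol does not answer the point. This article does state a justification, and that justification is wrong as written and concerns a secondary outcome.

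**Conclusion.** The point holds in this form. The stated sizes and the stated 80 % are inconsistent with the paragraph's own SD of weight loss: about 10 men and 9 women would suffice for a paired test (about 30 per sex if the SD doubled), and power at 179 and 159 is essentially 100 %. This rests on the inference about which SD was used and on reading 2.2 % as the SD of individual losses in both sexes.

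More important, the calculation does not bear on finishing time across diets, so the statement under Strengths of the study has no quantitative support. Power for that comparison is undetermined rather than shown to be poor. Under the assumed total of 338, detectable vegan-omnivore differences run from about 0.37 to 1.4 SD before covariate adjustment.

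**What to change.** - Withdraw 179 and 159 as the study's sample-size justification.
- If the weight-loss test is kept, label it secondary, name the SD, and restate it as a paired calculation with the 2.2 % SD and a sensitivity range for self-weighing in clothing and shoes.
- For the finishing-time comparison, choose the metric and state the difference detectable with 80 % power over a range of expected diet-group sizes, with the assumed SD and any covariate adjustment made explicit.
- Limit the claim under Strengths of the study to what those figures support.

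The cost is one reworded paragraph and one qualified sentence. The stated figure becomes less favourable, because a single 80 % is replaced by a range that depends on how many vegetarians and vegans take part.

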**Fig. 1 Fig1:**
[figure not shown]
Timescale of the NURMI Study

### Step 1

Epidemiological pre-study

Step 1 is composed of a short standardized online questionnaire for endurance and ultra-endurance runners (any distance and any level of performance) primarily in Austria, Germany and Switzerland. Data on sex, age, kind of diet, and running history and habits will be collected. We aim to approach as many runners as possible for this step since gathered data will be used to estimate the prevalence of vegetarians and vegans active in endurance running.

### Step 2

The major NURMI Study questionnaire

Runners matching inclusion criteria of the respective subgroups (capable of running a half-marathon etc./see “Subjects” section) complete an extended questionnaire on health status, specific dietary habits (details of consumption of specific foods or food groups), running history (i.e. preferred running distance, finished races overall and number of completed races in the last 2 years, preparation for a specific event, average distance and training load per day/week, etc.) and exercise induced diet (i.e. during training, racing or a day of rest, nutritional strategy on race day, etc.) as well as quality of life and health-related behavior. Step 2 includes a short form of the Quality of Life questionnaire (QOL BREF 26) distributed by the World Health Organization.

### Step 3

NURMI post-race testing

After individual finishing a race of at least half-marathon distance, runners complete a questionnaire on final ranking, finishing time, energy and fluid intake, in race dietary strategy, and physical and mental perception. The rate of perceived exertion (RPE, overall, leg muscles and respiratory system) will be assessed by using the Borg Scale (Borg 1998).

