#### Further measurements

Individual finishing time will be measured by the running events professional timing system and will be calculated as percentage of the overall winner’s time.

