#### Secondary outcomes

Outcomes from Step 1 are: nationality, sex, age, body weight, height, calculated BMI, kind of diet, attended races in past 2 years, finished running distances, personal best time on each distance, number of planned events for 2014/2015, in-race food and fluid consumption, daily/weekly training frequency, daily/weekly training load, period of preparation for main event, and aim of race participation.

Outcomes from Step 2 are: years of running experience, motivation for running then and now, assisted training, years of race experience, training intensity, medium/long-term goal of racing, additional specific kinds of training, specific diet including supplements, specific training/diet prior to race, diet on day of rest/training/race, pre/in/post-race diet, specific gear, relevant medical measures, and quality of life and health-related behavior.

Outcomes from Step 3 are: Pre-race: body weight (including clothing and shoes). In-race: individual finishing time, individual runtime as % of overall winners time (calculated), ranking, calculated pace, temperature, wind, air pressure, humidity, sunlight. Post-race: body weight (including clothing and shoes), calculated weight loss, RPE (Borg) whole body/respiratory/legs, mental mood, fluid and nutrient intake including breakfast, and dietary strategy during race.

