### Limitations of the study

Not all vegetarians and vegans participating in running events may be within the reach of the various recruitment methods. Due to various season, daytime and location of races, environment conditions (e.g. weather including sun or rain, temperature, relative humidity) will vary among the respective running events. Furthermore, our study shares with others the limitation of the cross-sectional design; therefore the present investigation allows no conclusion regarding causality. Prospective cohort studies are needed to confirm the associations between specific kinds of diet, health status and endurance performance to assess the causal direction and to develop recommendations for nutritional intake for vegetarian and vegan runners for training and racing.

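### The diet-only ANOVA compares percent of the overall winner's time, ranking and pace across self-chosen races, so sex mix and field size can appear as a diet difference

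*Protocol article*

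**What the plan says.** Further measurements sets the scale: "Individual finishing time will be measured by the running events professional timing system and will be calculated as percentage of the overall" winner's time. It does not mention a winner by sex or age class.

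Statistical methods then names two analyses of performance.

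- **Regression.** The outcome, "individual finishing time (% of overall winners time, ranking, calculated pace"), is regressed on diet, sex, age, BMI, running and race history, training variables and in-race intake.
- **ANOVA.** "An analysis of variance will be performed to compare individual finishing time (% of overall winners time, ranking, calculated pace), sex, age" and a long list of other characteristics "among the three subgroups created respective to diet". Here sex and age are further variables to be compared, not covariates.

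The races differ from runner to runner. Step 3 takes whichever race of at least half-marathon length the runner has finished, and Inclusion criteria admits both half-marathon and marathon. Limitations of the study accepts that "environment conditions (e.g. weather including sun or rain, temperature, relative humidity) will vary among the respective running events". Secondary outcomes lists what Step 3 records: "ranking, calculated pace, temperature, wind, air pressure, humidity, sunlight". No weather item appears as a covariate in either analysis.

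**The concern.** Comparing performance by diet is the first goal under Trial objectives. A three-group comparison on diet alone is fair only if the groups are alike in whatever else moves the score, or if the score removes it. Three things are left in.

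1. **Sex.** One reference per race serves both sexes. If women are on average slower than men, a diet group with more women scores worse even when diet has no effect.
2. **Field size.** A finishing place means something only relative to the number of finishers, and no scaling is stated.
3. **Event, distance and weather.** Pace depends on the distance raced, the course and the conditions. None of these is in either analysis. The regression has finished running distances, but Secondary outcomes lists that item under Step 1, as running history, so it is not clearly the distance of the Step 3 race.

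At stake is a reported diet difference, or the absence of one, that reflects who entered which race. Strengths of the study relies on large numbers to detect differences. A bias of fixed size becomes easier to detect as numbers grow.

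**Working it through.** **Plan figures.** The plan gives no figure for this point. Its only sample sizes, 179 men and 159 women, concern weight loss during the race and are not used here.

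**Sex artefact in the ANOVA**

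Inputs, all assumed because the documents give none: men average 170 % of the overall winner's time; women are slower by a fraction g of 0.08 to 0.12; the share of women differs by d between two diet groups; diet has no effect.

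A group with a share p of women has mean score 170(1 − p) + 170(1 + g)p = 170(1 + gp). The difference between two groups is therefore 170 × g × d.

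| d | g = 0.08 | g = 0.12 |
|---|---|---|
| 0 | 0 | 0 |
| 0.10 | 170 × 0.08 × 0.10 = 1.4 | 170 × 0.12 × 0.10 = 2.0 |
| 0.20 | 170 × 0.08 × 0.20 = 2.7 | 170 × 0.12 × 0.20 = 4.1 |
| 0.30 | 170 × 0.08 × 0.30 = 4.1 | 170 × 0.12 × 0.30 = 6.1 |

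Units are percentage points of the winner's time. The result is proportional to each input.

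**Effect on the false-positive rate**

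Further assumptions: SD 25 points within sex, 40 % women in the first group, 40 % + d in the third, the second midway, and g of 0.10 to 0.12. Simulated rejection rates at a nominal 5 % with no diet effect:

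| d | Diet-only ANOVA, 100 per group | Diet-only ANOVA, 300 per group |
|---|---|---|
| 0 | about 5 % | about 5 % |
| 0.10 | 7-8 % | 10-12 % |
| 0.20 | 11-16 % | 26-37 % |
| 0.30 | 21-28 % | 57-70 % |

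With sex added to the model, the rate in the unbalanced settings is 3.7-5.4 %, that is, about nominal.

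**Ranking.** A mid-field finisher is 100th in an assumed field of 200 and 10,000th in an assumed field of 20,000. The relative performance is the same and the ranks differ by a factor of 10,000 / 100 = 100. Neither analysis has a term that absorbs this.

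**Dependence on one winner.** An assumed 240-minute marathon scores 240 / 130 = 185 % against a 130-minute winner and 240 / 160 = 150 % against a 160-minute winner. Neither analysis has a term for this.

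**Which fault touches which measure**

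| Measure | Sex | Field size | Distance, course, weather |
|---|---|---|---|
| % of overall winner's time | ANOVA only | no | largely removed by scaling within the event, but depends on one winner |
| Ranking | ANOVA only, if rank is overall | both analyses | indirectly, through the event |
| Pace | ANOVA only | no | both analyses |

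**The case against.** The strongest reply is that diet effects are to be estimated by the regression, which contains sex and age. The ANOVA sentence runs from finishing time through height and motivation to gear, so it can be read as a descriptive comparison of groups. The first part stands: the sex artefact does not reach the regression. The second is plausible, but the article does not call the ANOVA descriptive, and it yields a test of finishing time by diet with no adjustment.

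A reader might also infer more than the text supports:

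- **That all three measures suffer equally from race conditions.** They do not. Percent of winner's time is scaled within the event and so already removes part of the course and weather effect. The point bears mainly on pace, and field size on ranking.
- **That the source of finishing time is contradictory.** Step 3 says "runners complete a questionnaire on final ranking, finishing time, energy and fluid intake", while Further measurements refers to the event's timing system. A runner who reports the official time satisfies both.
- **That the three measures are rival versions of the primary outcome with no lead.** Primary outcomes names the Step 3 marathon finishing time, adjusted to performance level. Percent of winner's time, ranking and pace are listed under Secondary outcomes.
- **That the article prescribes raw overall ranks.** It says only ranking. It neither states nor excludes class rank or scaling by field, and a fuller document could add either.

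Finally, every input to the sex calculation is assumed, and the artefact vanishes with equal sex mix.

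**Conclusion.** The point holds in limited form. The overall-winner reference and a diet-only ANOVA are both stated choices, and together they let a sex imbalance between diet groups appear as a diet difference. Under the assumed 170 % and 8-12 %, this is about 1.4-2.0 points for a 10-point imbalance and 2.7-4.1 for 20 points. The documents do not show whether any imbalance will occur. The documents do not support extending this to the regression, which includes sex.

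For field size, event, Step 3 distance and weather, the gap is in both analyses as described. It matters mainly for ranking and pace. The size cannot be given, because it depends on which races each diet group enters.

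This should be corrected before analysis. It does not invalidate the design.

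**What to change.** 1. **Further measurements and Statistical methods:** score finishing time against a same-sex reference for the same event and distance. The same-sex winner removes the sex artefact but still depends on one runner. The same-sex median finisher avoids that.
2. **Ranking:** replace it by percentile rank within event, distance and sex.
3. **Test of diet on performance:** state that it is the covariate-adjusted regression, and label the ANOVA of finishing time descriptive.
4. **Pace:** add the Step 3 race distance and the recorded conditions to its regression.

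The cost is looking up public results for each race (same-sex reference and number of finishers by sex), some rewording and a little more analysis. It asks nothing more of participants, since the weather items are already planned. Schedule of the study puts analysis after the questionnaires close on 31 December 2015, so the change can be made before any results are seen.

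### Analysis of variance and mean ± SD are assigned to items that are nominal as named, and mean ± SD also to diet prevalence, so some comparisons would depend on arbitrary category codes

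*Protocol article*

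**What the plan says.** Statistical methods in the protocol article names a single method for comparing omnivorous, vegetarian and vegan runners. The sentence opens "An analysis of variance will be performed to compare individual finishing time" and runs through sex, age and several dozen further items. Among them are "aim of race participation, years of running experience, motivation for running then and now, assisted training" and, later, "specific gear, relevant medical measures, pre/post-race body weight". It closes with "mood status, and RPE (Borg) whole body/respiratory/legs, among the three subgroups created respective to diet". Racing goals, additional kinds of training and in-race nutritional strategy are also in the list.

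On reporting, the section states one format without exception: "All data derived from the statistical methods will be given in mean ± standard deviation".

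The only other analysis named is a regression with finishing time as the outcome. The section mentions no frequencies, percentages or contingency-table method.

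Under Primary outcomes, beside finishing time, "the primary outcome is the prevalence of kinds of diets (omnivorous, vegetarian, vegan) among runners attending running events". The description of Step 1 says its data will be used to estimate that prevalence.

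**The concern.** Analysis of variance compares group means. For age, weight or pace, the mean is the quantity of interest. For an item such as race aim or motivation, the answers are labels, and a mean exists only after someone numbers them. The numbering is arbitrary, so the group means, the F statistic and the p-value are arbitrary too. A clear difference between diet groups can disappear because of the order in which the questionnaire lists its answers.

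The reporting rule has the same flaw. Mean ± SD of a category code tells the reader nothing, and for a proportion the SD is fixed by the proportion itself. Taken literally, the rule gives an unsuitable summary to one of the two primary outcomes.

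This is not detail left to an analysis plan. The article assigns the method and the format, so a later plan using chi-square tests and percentages would contradict it rather than complete it.

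**Working it through.** The article gives no figure on this point to reproduce. Its sample sizes concern body-weight loss and do not enter here. The check has three parts, all with assumed inputs because the questionnaires and achieved numbers are not shown.

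**1. Dependence on coding.** Assume 100 runners per diet group and one unordered item with categories A, B and C. The counts are 30/40/30 in groups 1 and 2, and 45/10/45 in group 3.

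- Codes A = 1, B = 2, C = 3. Group means: (30×1 + 40×2 + 30×3)/100 = 2.0, again 2.0, and (45×1 + 10×2 + 45×3)/100 = 2.0. The between-group sum of squares is 0, so F = 0 and p = 1.0.
- Codes A = 2, B = 1, C = 3. Group means: 1.90, 1.90 and 2.35; overall mean 2.05. Between-group sum of squares = 100 × (0.15² + 0.15² + 0.30²) = 13.5. Within-group sum of squares = 69 + 69 + 42.75 = 180.75. F = (13.5/2)/(180.75/297) = 11.09, p = 0.000023.
- Chi-square, any coding. Expected counts are 35/30/35 in each group. Groups 1 and 2 each contribute 25/35 + 100/30 + 25/35 = 4.76. Group 3 contributes 100/35 + 400/30 + 100/35 = 19.05. The total is 28.57 on 4 degrees of freedom, p = 0.0000096.

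The data are identical throughout; only the labels change.

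**2. Power and type I error by simulation.** Three groups of 100, a four-category item, 4,000 runs, test level 5 %. Assumed distributions: 40/10/10/40, 10/40/40/10 and 25/25/25/25 %.

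| Codes for the four categories | ANOVA rejects | Chi-square rejects |
|---|---|---|
| 1, 2, 3, 4 | 0.05 | 1.00 |
| 1, 4, 2, 3 | 0.94 | 1.00 |
| 1, 3, 4, 2 | 1.00 | 1.00 |
| 1, 2, 3, 4, no true difference | 0.0485 | 0.049 |

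For a two-category item coded 0/1 with no true difference (groups of 120, 40 and 40), both tests reject in 0.051 of runs.

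**3. Mean ± SD for a prevalence.** SD = √(p(1 − p)). Background gives 1.1 % vegan and 10 % vegetarian for Germany; assume N = 1,000.

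- p = 0.011: SD = √(0.011 × 0.989) = 0.104, reported as 0.011 ± 0.104. The Wilson 95 % interval is 0.6 % to 2.0 %.
- p = 0.10: SD = √(0.10 × 0.90) = 0.30, reported as 0.10 ± 0.30. The Wilson interval is 8.3 % to 12.0 %.

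The SD depends only on p, not on N, so it says nothing about precision.

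**The case against.** The strongest reply is that the harm is narrower than the long list suggests. Several parts of it stand.

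- Analysis of variance suits the continuous items, and its use for Borg ratings, mood, counts or ranks is defensible with large numbers. Insisting on rank tests or Welch's version there would be preference.
- Sex, and assisted training if it is answered yes/no, lose almost nothing, as the two-category check shows.
- The example is built so that the coded means coincide. It shows what can happen, not what to expect.
- Item types are read from their names. Motivation or goals might turn out to be rating scales.

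Stronger readings are also tempting, and the document does not support them.

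- A reader might infer that every variable goes through this one test. A regression is also planned for finishing time, and nationality, quality of life and weather are not in the list.
- A reader might infer that the coding manufactures false differences. With no true difference, the error rate stays near 5 %; what fails is power and interpretation.
- A reader might infer that comparing diet items across diet groups is circular and that they should be removed. Trial objectives makes validation of self-reported diet the third goal, these comparisons may serve it, and nothing shows that the groups are built from the same items.
- A reader might infer a 92 % chance of at least one false positive (1 − 0.95^50). That needs about 50 independent tests with every null true. Weight, height and BMI, or time, pace and ranking, are plainly dependent, and the 5 % level is stated only for the sample size.
- A reader might infer that prevalence will have no confidence interval. The article does not say so, and an interval method is detail that an article may leave out. The stated error is only the conflict between one format for all data and a proportion.

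**Conclusion.** The section is wrong as written, and the wording should be changed. It assigns a comparison of means to items that are nominal as named, and a mean ± SD summary to all data, including categorical items and a primary outcome that is a proportion. For unordered items with more than two categories, the result depends on arbitrary numbering: p = 1.0 or 0.000023 in the constructed example, and rejection in 0.05 to 1.00 of simulated runs, against about 1.00 for chi-square.

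The conclusion assumes that items such as race aim, motivation, goals, gear and nutritional strategy are recorded as unordered categories. The numbers rest on assumed distributions with 100 runners per group and show the range of possible effects, not a forecast. Type I error is not affected, nor is the comparison of finishing time.

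**What to change.** Reword Statistical methods as follows:

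- Restrict analysis of variance and mean ± SD to continuous variables and to scales that can reasonably be treated as such.
- Compare nominal items across diet groups with chi-square tests, or Fisher exact tests where counts are small, and report n and %.
- Report diet prevalence as n, % and a 95 % CI.
- Label the long list of secondary group comparisons as exploratory.
- Keep the diet items in the list, because they may serve the validation goal.

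The cost is a few sentences. The tests are standard in the named software, no data item changes, and Schedule of the study places analysis after data collection closes.
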